### Explorative analyses

The analyses will be conducted in accordance with the intention to treat (ITT) principle. Missing data will be imputed using state of the art imputation methods, a reliable method for handling missing values [35]. In addition, per protocol analyses will be conducted; if equal clinical effects are found, such analyses are more conservative than ITT [67].

Outcomes for continuous variables, such as severity of depressive symptoms and mastery, at T1, T2 and T3 (Week 10, 20, and 30) are estimated for descriptive purposes through mixed-model analyses (MM), with participants as random effects, and time (T1-T3), group (bCBT vs. CBTAU) and time x group as fixed effects, with baseline scores as a single covariate. To assess the magnitude of treatment effects, within and between-group Cohen’s *d* effect sizes [68] for each time point are calculated by dividing MM parameter estimates of fixed effects at each post-treatment assessment by the pooled standard deviation of outcome measurements at baseline (T0). Effect sizes under 0.2 are deemed to be small, 0.5 are deemed moderate and 0.8 are deemed to be large [68].

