## Methods

### Study design

The pilot study is designed as a randomized controlled trial with two parallel groups (N = 150). Participants will be randomized to either blended CBT (bCBT) or usual face-to-face CBT (CBTAU). Participants in both groups will complete assessments at baseline and at three fixed 10-week intervals after the first treatment session (Week 10, 20 and 30).

The design incorporates the ISPOR RCT-CEA Task Force recommendations for cost-effectiveness analyses alongside clinical trials and the ISPOR Consolidated Health Economic Evaluation Reporting Standards (CHEERS) [31-33]. The protocol for this study has been approved by the Medical Ethics Committee of the VU University Medical Centre (Registration number 2014.191). Written informed consent will be obtained from all participants. Figure 1 displays the flowchart of the study design.

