#### Cognitive behavioural treatment-as-usual (CBTAU)

In the CBTAU condition, patients receive, on average, twenty 45-minute sessions of face-to-face CBT over 20 weeks (one session per week). Therapists follow an established face-to-face CBT protocol [39] that contains the components referred to above. Therapists are required to include all four elements of CBT, but are free to decide how many sessions are spent on each module.

All individual sessions should involve monitoring of depressive symptoms, addressing the week gone by and current issues, and discussing information and homework exercises for the previous week and the week to come. Sessions will be concluded with a summary and evaluation. Patients receive their homework exercises on paper.

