#### Blended cognitive behavioural treatment (bCBT)

For the bCBT group, the existing CBT protocol [39] is divided over ten 45-minute face-to-face sessions and nine online sessions. The treatment will be delivered over a period of ten weeks (one face-to-face and one online session per week). Treatment starts and ends with a face-to-face session. The therapist follows a fixed treatment protocol. The blended face-to-face sessions are structured in a similar way to the regular face-to-face sessions, leaving the therapist room to respond to the individual patient’s needs in each session. During the sessions, the patient and therapist are logged in on the personal patient environment in the online platform.

The online platform is a secure web-based environment (Minddistrict; www.minddistrict.com). Patients and therapists access this platform with a personalized login. The website offers information that reinforces and develops on the content of the face-to-face sessions. A short video fragment is included in each online session in which a therapist explains the theory in lay terms.

In addition, patients use the website to complete homework exercises, such as monitoring their activities, feelings, thoughts and behaviour. Testimonials from two fictional patients are provided to give insight in how the exercises can be executed.

Therapists monitor their patients’ online progress and provide feedback each week before the next face-to-face session. The feedback messages take approximately 15 minutes to write and are sent on the online platform to ensure secure communication.

On completion of treatment, patients can continue to access the online treatment platform to reread information and look up homework exercises, such as the relapse prevention plan.

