### Sample size

Given the nature of our pilot study, we chose to conduct a cost-effectiveness study, in which we focus on the probability of cost-effectiveness of bCBT in comparison with CBTAU for various ‘willingness to pay’ ceilings, i.e., the cost-effectiveness acceptability curve (CEAC; Fenwick et al. 2001). The probabilistic assessment does not entail hypothesis testing. Instead, the outcomes will be presented as the likelihood (in %) that bCBT is superior to CBTAU in terms of cost-effectiveness [18].

Through a simulation study, we determined the impact of various sample sizes on the stability of the CEAC. Using realistic fixed estimates of the mean and standard deviation of effects and costs at population level (based on Hakkaart-van Roijen et al., 2006), we simulated a large number of trials in which we systematically varied sample sizes between n = 10 to n = 500 per group (n = 10, 25, 50, 75, 150, 500). As expected, the stability of the CEAC improved with increasing sample size. Below n ≤50, probability estimates were highly unstable. At a sample size of n = 75 per group, however, we found probability estimates to converge to acceptable 75% percentile ranges within the relevant range of willingness to pay ceilings. Therefore, for this study, we settled for a sample size of N = 150 (n = 75 per group).

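### The descriptive mixed model allows one variance, one correlation and one baseline slope for weeks 10, 20 and 30, so visit-specific intervals are miscalibrated if adjusted variance changes over follow-up

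*Protocol article*

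**What the plan says.** The model stands in the protocol article under Explorative analyses. Continuous outcomes at T1, T2 and T3, such as depression severity and mastery, "are estimated for descriptive purposes through mixed-model analyses (MM"). The terms are then listed: the model is fitted "with participants as random effects, and time (T1-T3), group (bCBT vs. CBTAU) and time x group as fixed effects". Baseline enters as one further term, in the article's words "with baseline scores as a single covariate". The listed terms do not include baseline x time, a random slope or a residual covariance structure. The fixed-effect estimates at each follow-up visit are turned into Cohen's d using the pooled baseline SD, so the model's product is a set of visit-specific contrasts.

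The three visits fall at different stages of treatment. For blended CBT, "The treatment will be delivered over a period of ten weeks". Usual CBT is, on average, "twenty 45-minute sessions of face-to-face CBT over 20 weeks". Week 10 is therefore the planned end of treatment in one arm and the halfway point in the other, week 20 is the end of usual CBT, and week 30 is follow-up for both.

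**The concern.** A participant random intercept with independent, equal-variance residuals implies compound symmetry. The variance is the same at all three visits, and weeks 10 and 30 are as strongly correlated as adjacent visits. One baseline term without a time interaction implies that baseline predicts week 30 as strongly as week 10. These are strong assumptions when the visits are not exchangeable, and the article gives no reason for them.

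The practical result is that three visit-specific variances are averaged and the average is applied to every contrast. Reported precision would be too poor at some visits and too good at others, and nothing in the output would show it. The pilot is meant to inform whether a fully powered clinical and economic trial is worthwhile, so the precision attached to its clinical estimates has some bearing on that decision.

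**Working it through.** **The plan's own figure.** The only related figure is the sample size: 2 x 75 = 150, which agrees. The simulation behind 75 per group cannot be rerun, because its means and SDs for costs and effects are not given. The article states no standard error for the mixed model.

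**Inputs from the article.** n = 75 per arm (Sample size), 1:1 allocation (Randomization and blinding), visits at weeks 10, 20 and 30 (Study design), and the model terms (Explorative analyses).

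**Assumed inputs.** Complete data, baseline SD = 1, follow-up SDs s_t, and correlations r_t with baseline. None of these is in the article, so a range is shown.

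**Formulas.**
- Visit-specific baseline slope: b_t = r_t x s_t. The common slope b is the mean of the three.
- Adjusted variance at visit t: v_t = s_t² - 2 b b_t + b².
- Standard error given by the stated model, at every visit: sqrt(2 x mean(v_t) / n).
- True standard error at visit t: sqrt(2 v_t / n).
- Coverage of a nominal 95% interval: 2Φ(1.96 x model SE / true SE) - 1.

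**Worked case, row d.** SDs 1/1.15/1.3 and correlations 0.6/0.5/0.4 give slopes 0.600/0.575/0.520, with mean 0.565 and b² = 0.319.
- v_10 = 1 - 0.678 + 0.319 = 0.641
- v_20 = 1.3225 - 0.650 + 0.319 = 0.992
- v_30 = 1.69 - 0.588 + 0.319 = 1.422
- Mean = 1.018, so the model SE is sqrt(2 x 1.018 / 75) = 0.165 at each visit.
- True SEs are 0.131, 0.163 and 0.195.

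**All cases** (weeks 10/20/30; SEs in baseline-SD units):

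| | SD | Baseline correlation | Model SE | True SE | Model/true | Coverage, % |
|---|---|---|---|---|---|---|
| a | 1/1/1 | .5/.5/.5 | 0.141 | 0.141/0.141/0.141 | 1.00/1.00/1.00 | 95/95/95 |
| b | 1/1/1 | .6/.5/.4 | 0.141 | 0.132/0.141/0.151 | 1.07/1.00/0.94 | 96.5/95.0/93.4 |
| c | 1/1.1/1.2 | .5/.5/.5 | 0.156 | 0.142/0.156/0.170 | 1.10/1.00/0.92 | 96.9/95.1/92.8 |
| d | 1/1.15/1.3 | .6/.5/.4 | 0.165 | 0.131/0.163/0.195 | 1.26/1.01/0.85 | 98.6/95.3/90.3 |
| e | 1.2/1.1/1 | .5/.5/.5 | 0.156 | 0.170/0.156/0.142 | 0.92/1.00/1.10 | 92.8/95.1/96.9 |
| f | 1.2/1.1/1 | .6/.5/.4 | 0.156 | 0.159/0.156/0.152 | 0.98/1.00/1.02 | 94.5/95.0/95.5 |
| g | 1/1.2/1 | .5/.5/.5 | 0.152 | 0.142/0.170/0.142 | 1.07/0.89/1.07 | 96.4/91.9/96.4 |

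Adjusted variance rises in rows b to d, falls in e, is nearly constant in f and peaks at week 20 in g.

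**Simulation check.** Random-intercept models were fitted to 200 simulated trials per case, with a correlation of 0.7 between adjacent visits. The simulation error on coverage is about 1.5 points, from sqrt(0.95 x 0.05 / 200).
- Row d: average model SE 0.164 at every visit, coverage 98/95/89.5%.
- Row e: average model SE 0.156 at every visit, coverage 91.5/94.5/97.5%.
- Row a: average model SE 0.142 at every visit, coverage 96.5/97/96.5%.

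The simulated spread of the week-30 estimate in row d was 0.216 against 0.195 by formula, about two simulation standard errors apart. The coverage agrees.

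**With the fix.** Visit-specific slopes and variances give SE = sqrt(2 s_t²(1 - r_t²) / n). This is 0.131/0.141/0.150 in row b and 0.131/0.163/0.195 in row d. True precision barely moves. What changes is that the reported standard error matches it.

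**The case against.** **The covariance is not stated.** The article names no residual structure, and a condensed article may leave that to an analysis plan that is not shown. Many mixed models pair random effects with a separate residual structure, and a single covariate may mean only that baseline is the sole covariate. This stands in part. The point is therefore limited to the ordinary reading, and it cannot be said that the text forces equal variance. But the terms are listed, and the ordinary reading of that list is a random intercept with one slope.

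**The direction is unknown.** A reader might infer that intervals are too wide at week 10 and too narrow at week 30. The article does not support that as a fact. It requires adjusted variance to rise from week 10 to week 30. Entry with major depression and later spread concerns baseline to follow-up, whereas baseline is only a covariate here. The staggered end of treatment suggests that variance may differ between visits, not which way. This objection stands in full.

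**Dropout.** A reader might also infer that the week-30 estimate is biased by dropout. The article plans imputation and gives no dropout rate or mechanism, so there is no basis for that claim.

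**The consequence is small.** The model is exploratory and descriptive, no hypothesis is tested with it, and its stated product is Cohen's d rather than an interval. The economic results use treatment response, diagnostic status and QALYs with bootstrapped cost-effectiveness ratios, and do not draw on this model. This stands, and it sets the severity.

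**Conclusion.** The point holds in conditional form and is minor. On its ordinary reading, the stated model gives essentially the same standard error at weeks 10, 20 and 30, whatever the visit-specific variances are. If adjusted variance is not constant, any visit-specific intervals are miscalibrated.

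Under the assumed patterns in which it rises (rows b to d), the standard error is 7-26% too large at week 10 and 6-15% too small at week 30, with week-30 coverage of 90-93%. If it falls (row e) the error reverses, with 92.8% coverage at week 10. It can also peak at week 20 (row g, 91.9%), nearly cancel (row f) or be absent (row a). All these sizes rest on assumed SDs and correlations and on complete data.

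With complete data the estimated group differences are not biased. It would be wrong to conclude that the cost-effectiveness or cost-utility results are affected, even though week 30 is also the horizon of the economic evaluation.

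**What to change.** Keep time, group and time x group as fixed effects. Replace the single participant random effect with an unstructured within-patient covariance matrix for T1 to T3, and add baseline x time. Report the between-group differences and Cohen's d at weeks 10, 20 and 30 from that model. This does not depend on guessing the variance pattern, since it is valid in every row of the table.

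The cost is one line of text and six parameters: an unstructured 3 x 3 matrix has six against two for the random intercept and residual (four more), and baseline x time adds two slopes. That is affordable with 150 patients. Intervals may become somewhat wider at visits where the pooled variance was too small; in the most marked case tried (row d), the week-30 standard error goes from 0.165 to 0.195. Where variances and slopes really are constant, little is lost. If a fuller analysis plan already specifies this structure, aligning the two texts is enough.

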## Discussion

Major Depressive disorder is a highly prevalent disorder, with a major impact on personal, professional and family life and is associated with considerable medical and non-medical costs. In order to ensure the availability of affordable evidence-based treatments in the future, investing in the development of cost-effective treatments is warranted. This is especially relevant in specialized mental health care, as treatment in this sector tends to be intensive and of a long duration.

Blended care may offer a way to improve the cost-effectiveness of depression treatment. This type of treatment combines elements of online and face-to-face treatment, with the goal of diminishing the number of face-to-face sessions needed to deliver the treatment protocol.

### Strengths and weaknesses

In the proposed study, integrated blended cognitive behavioural treatment will be compared with face-to-face cognitive behavioural treatment for major depression. To the best of our knowledge, this is one of the first studies to evaluate this type of blended treatment in an outpatient specialized mental health care setting. Therefore, the trial is designed as a cost-effectiveness study to assess the probability that blended CBT is cost-effective in comparison with face-to-face CBT in the short term (30 weeks) by way of proof-of-concept. The results of the study provide information on the possible strengths and benefits of blended CBT and will support decision-making on whether an adequately powered clinical and economic randomized controlled trial of blended treatment for depression in routine practice is advisable and feasible. By carrying out budget impact analyses, we aim to inform stakeholders from various perspectives, including patients, mental health service providers and health insurers.

In order to facilitate the decision-making process, the study is designed to closely adhere to established procedures in routine practice in outpatient specialized mental health care. This is reflected in the decision to deliver blended CBT over a ten-week period, while adhering to the usual time frame of 20 weeks for the face-to-face CBT. Two factors explain this choice in relation to blended CBT. First, providing online and face-to-face sessions within the same week is common practice in the context of guided online treatment. Second, a recent meta-analysis by Cuijpers et al. [69] showed that intensifying face-to-face treatment from one to two sessions a week might be beneficial in terms of clinical results, with an increase in effect size of *g* = 0.45. In the proposed study, the reason not to match the intensity of treatment as usual is that this would deviate from current practice, therefore undermining the goal of the proposed study. As a result, any clinical results will be harder to attribute to the blended intervention. However, the aim of this pilot study is to gain insight into the implementation value of blended CBT, rather than clinical effectiveness.

In summary, blended cognitive behavioural treatment (CBT) for major depression might be more cost-effective than face-to-face CBT as usual, while maintaining clinical effects. The proposed study is designed to contribute to the body of knowledge on the possible value of blended treatment for depression when applied in outpatient specialized mental health care. It aims to underpin future decisions on whether further research on blended treatment for depression in routine practice is advisable and feasible.

### Trial status

The trial is in the on-going recruitment phase.
